### Statistical analysis

Primary outcome is the occurrence of HAP within the first 28 days after randomization. The primary analysis will use a Cox multivariate proportional hazards model that includes 2 predefined covariable: MGAP [15] and Coma Glasgow Score. We will also perform complementary sensitivity analyses with an adjustement on etomidate use. Corresponding hazard ratios (HRs) along with their 95% confidence intervals (CIs) will be reported. The crude percentages and the Kaplan-Meier estimators will also be presented. Cumulative incidence will also be estimated for the primary outcome by treating deaths as competing risks. The Fine and Gray model [16] will be used. If a difference is confirmed for the primary endpoint, sub-group analysis for multiple trauma (presence or absence), hyporeactivity to adrenocorticotrophic hormone (presence or absence), early treatment administration (<18 hours after trauma or >18 hours) will be performed. In order to control the family wise error rate, a stepwise hierarchal testing procedure will be used for subgroup analyses.

Normally distributed variables will be expressed as mean and standard deviation; non-normally distributed variables will be expressed as median and inter quartile ranges. Categorical variables will be expressed as numbers and percentage, as well as the absolute difference (95% CI). Linear or logistic regressions will be used as appropriate for the secondary endpoints.

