### Randomization

Patients eligible for inclusion should be randomized, and the study treatment is started within the first 24 hours. Patients are randomized in a 1:1 ratio in fixed blocks of 12 and stratified according to the center and MGAP score [15] by a computerized number generator list provided by a statistician not involved in the determination of eligibility or in the assessment of outcomes. All assignments are made through a dedicated, pass-word protected, SSL-encrypted website. Randomized patients are given a number corresponding to a «Corti-TC treatment pack» that contains: 20 × 100 mg vial of hydrocortisone or placebo, 10 pills of 50 μg of fludrocortisone or placebo and a sheet for schedule administration.

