### Statistical consideration

The required sample size is calculated from results of the HYPOLYTE study [10]. The power calculation is performed for comparison between the hydrocortisone and placebo groups in patients with corticosteroid insufficiency. The sample size needed to detect an absolute decrease in pneumonia incidence of 20% is 121 patients in each group, assuming a rate of 70% in the placebo group, in a 2-sided test performed with a statistical power of 90% and an α risk of 5%. Assuming a rate of 75% of corticosteroid insufficiency [10], 326 patients (approximately 163 patients in each group, and 41 patients with normal corticosteroid function who are untreated) are needed. Two a priori interim analyses using the O'Brien and Fleming method for α risk spending are planned respectively after the inclusion of 110 and 220 patients.

An ITT and a mITT analysis will be performed. Because the patients with adapted corticosteroid function are left untreated (when the cosyntropin test show no corticosteroid insufficiency), a modified intention-to-treat (mITT) analysis that includes only the patients with corticosteroid insufficiency is planned.

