Major modifiable risk factors for HAP as described by the American thoracic Society [23] are prospectively collected: oropharyngeal decontamination, proclive (>30°), stomach ulcer prevention, insulinotherapy, tracheostomy and protocol for sedation. All these factors can not be standardized in the protocol. Sedation is a cornerstone therapy for intracranial hypertension [24]. Therefore, it was not practical to perform either daily spontaneous breathing trials or daily liberation from sedation in a population of traumatic brain injury patients. Concerning tracheostomy, prevention of HAP by performing tracheostomy early is still debated. In a recent study, the incidence of HAP was similar in patients with early versus late tracheostomy [25]. None of the participating ICUs usually perform early tracheostomy or "daily spontaneous breathing" in TBI patients during the study period. Regarding insulinotherapy, tight glycemia control is a highly debated topic for ICU patients and is associated either with beneficial [26] or deleterious effects [27]. A tight glycemic control was not associated with any survival improvement of septic patients treated with hydrocortisone [28]. Proclive and oropharyngeal decontamination are commonly used in participating ICUs. Finally, a controlled double-blind randomized design may ensure the comparability of groups for the majority of interventions other than hydrocortisone infusion.

In this study, we use a placebo in a population of CIRCI patients. This point do not raise an ethical issue as the recommendations for the diagnosis and treatment of CIRCI recently published by the American College of Critical Care Medicine [29] state that: first, given the lack of data, treatment of CIRCI is not recommended in other population than septic shock patients; second, a call for studies in ICU populations other than septic patients (including trauma patients) was advocated. Moreover, a placebo is ethically justified because the placebo is given in addition to standard of care of TBI patients.

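### Randomisation is stratified by centre but the primary Cox model leaves centre out; if centres differ in HAP risk, this attenuates the hazard ratio, makes the test mildly conservative and costs some power

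*Protocol article*

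**What the plan says.** Protocol article, Randomization: patients are "randomized in a 1:1 ratio in fixed blocks of 12 and stratified according to the center and MGAP score".

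Protocol article, Statistical analysis: the primary analysis is "a Cox multivariate proportional hazards model that includes 2 predefined covariable: MGAP [15] and Coma Glasgow Score". The only further adjustment named for the primary outcome is in the next sentence: "We will also perform complementary sensitivity analyses with an adjustement on etomidate use". The Fine and Gray analysis is named without a centre term. Centre appears nowhere as a covariate, a stratum or a random effect.

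Protocol article, Discussion: the article lists modifiable HAP risk factors (oral decontamination, head-up positioning, ulcer prevention, insulin, tracheostomy, sedation protocol) and states "All these factors can not be standardized in the protocol". The same paragraph reports that positioning and decontamination are in common use at the participating units, and that none of them usually performs early tracheostomy or daily breathing trials in these patients.

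**The concern.** The randomisation uses two stratification factors. One (MGAP) is carried into the primary model and the other (centre) is dropped, with no reason given. Stratifying by centre makes the arms more alike within centres than chance would. If centre predicts HAP, a model that ignores it has two consequences:

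- Under the null, the model-based standard error is larger than the true sampling variation, so the test rejects less often than its nominal 5%.
- Under an effect, the Cox hazard ratio that does not condition on centre lies closer to 1 than the within-centre hazard ratio, because hazard ratios are non-collapsible.

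Both reduce power. The sample size is set for 90% power and the article states no margin for such a loss.

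**Working it through.** **1. The plan's own figures (Statistical consideration).** Inputs: "assuming a rate of 70% in the placebo group", a 20-point absolute reduction, two-sided 5%, 90% power, and 75% with corticosteroid insufficiency.

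- Per group, unpooled variance: (1.960 + 1.282)² × (0.7×0.3 + 0.5×0.5) / 0.2² = 120.8, so 121. This matches the stated figure.
- Total: 242 / 0.75 = 323, against 326 stated (within 3%). The check uses 326; the abstract gives 376.
- Implied hazard ratio under proportional hazards: ln(0.5)/ln(0.3) = 0.576.
- Expected events: 121 × (0.7 + 0.5) = 145. Schoenfeld's formula needs 138 for 90% power, and 145 events give 91.4%.

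**2. Assumptions that the article does not supply.** 10 or 20 centres of unequal size; two MGAP levels; normal centre effects on the log hazard with SD 0, 0.3, 0.5 or 0.8. To show what these mean, take a centre at 70% HAP and move its log hazard by one SD, using 1 − 0.3^exp(±SD):

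- SD 0.3: 59% to 80%
- SD 0.5: 52% to 86%
- SD 0.8: 42% to 93% (and 22% to 99.7% for the central 95% of centres)

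**3. Simulation.** 326 patients are allocated in blocks of 12 within centre × MGAP, a random 75% are analysed, and follow-up is censored at 28 days. The Cox model with MGAP and Glasgow score is compared with the same model plus a centre frailty of known variance (1,500 runs per cell). Deaths and interim looks are not simulated. Each cell shows centre omitted / centre frailty, with a true hazard ratio of 0.576 for the hazard ratio and power columns.

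| SD | Centres | Hazard ratio | Type I error | Power |
|---|---|---|---|---|
| 0.3 | 10 | 0.584 / 0.574 | 4.7% / 4.9% | 90.8% / 91.5% |
| 0.3 | 20 | 0.583 / 0.573 | 4.9% / 5.0% | 90.0% / 91.0% |
| 0.5 | 10 | 0.602 / 0.575 | 4.5% / 5.1% | 88.7% / 91.3% |
| 0.5 | 20 | 0.602 / 0.573 | 4.3% / 5.1% | 87.1% / 90.2% |
| 0.8 | 10 | 0.634 / 0.575 | 4.0% / 5.4% | 79.1% / 91.1% |
| 0.8 | 20 | 0.637 / 0.573 | 3.8% / 5.5% | 78.1% / 89.9% |

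The Monte Carlo standard error is about √(0.05×0.95/1500) = 0.6 points for type I error and √(0.9×0.1/1500) = 0.8 points for power. With centre omitted, the null hazard ratio stayed at 1.00 in every cell.

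**4. The same model with the baseline hazard stratified by centre** (3,000 runs, no pooling of small centres). Power, omitted / stratified:

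- SD 0: 91.5% / 90.2% (10 centres), 92.1% / 89.2% (20)
- SD 0.3: 90.3% / 90.0% (10), 90.4% / 89.1% (20)
- SD 0.5: 88.6% / 90.4% (10), 88.1% / 88.7% (20)
- SD 0.8: 80.2% / 89.6% (10)

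**5. Where the loss comes from** (SD 0.8, 10 centres, from step 4). Under the null with centre omitted, the estimates vary with an empirical standard error of 0.142 while the model reports 0.155; that gap is the conservatism. Under the alternative, the omitted model averages ln(0.632) = −0.459 with model SE 0.166 and empirical SE 0.160, so power ≈ Φ[(0.459 − 1.96×0.166)/0.160] = Φ(0.83) ≈ 80%. The stratified model averages ln(0.574) = −0.555 with SEs 0.173 and 0.175, so power ≈ Φ[(0.555 − 1.96×0.173)/0.175] = Φ(1.23) ≈ 89%. Most of the loss is therefore attenuation of the hazard ratio.

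**The case against.** The strongest case against has four parts.

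- **The effect is conditional.** If centres do not differ, omission costs nothing: at SD 0 the planned model has power of about 92%. The Discussion describes similar practice on positioning, decontamination and tracheostomy, and all sites are level I trauma centres. The only HAP range in the article, 30% to 50% in the Background, is across cited sources rather than these centres; it spans a hazard ratio of ln(0.5)/ln(0.7) = 1.9. This stands. It is why the point carries an if, and why SD 0.8 should be read as an extreme. Sedation, insulin and ulcer prevention are not described as uniform, so some spread remains plausible.
- **Stratifying by centre may not help.** This stands too. Strata gain nothing at SD 0.3 and 1 to 2 points at SD 0.5. A frailty did at least as well as omission at every non-zero SD tested, although its variance was taken as known.
- **A hazard ratio that does not condition on centre is a different estimand, not a wrong one.** Correct, so the shift should be called attenuation of the within-centre hazard ratio.
- **Handling of centre belongs in the SAP.** Partly right: a frailty or strata would not contradict the two named covariates, and if the full SAP already has one, the point is settled. But the article names the primary model's covariates explicitly, carrying over one randomisation factor and not the other.

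A reader might infer more: that the treatment comparison is confounded by centre, or that the test is unsound. The documents do not support either. Allocation is balanced by centre by design, and type I error with centre omitted never exceeded nominal beyond simulation noise. A reader might also expect a much lower type I error. Block-randomising the analysed patients directly within centre gives 2.7% to 3.5%, but the trial randomises everyone within centre × MGAP and about 75% are then analysed. Balance in the analysed set is therefore looser, and 3.8% to 4.5% is the better estimate.

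**Conclusion.** The point holds as a conditional loss of efficiency. The stated primary model drops a factor used in the randomisation. If centre is prognostic for HAP, the within-centre hazard ratio is attenuated, the test is mildly conservative and some power is lost. A positive result would remain valid; the risk is a missed or understated effect.

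The size rests on assumed numbers of centres (10 to 20) and an assumed spread, because the article gives neither. Against a centre frailty, the loss is about 1 point of power at SD 0.3, which is negligible and near simulation noise. It is about 3 points at SD 0.5 (hazard ratio 0.60 instead of 0.57 to 0.58; type I error 4.3% to 4.5%) and about 12 points at SD 0.8 (hazard ratio 0.63 to 0.64; type I error 3.8% to 4.0%). The change is worth making because it is nearly free, not because the planned analysis is invalid.

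**What to change.** In Statistical analysis, add centre to the primary Cox model as a shared frailty (random effect) and keep MGAP and Glasgow score as covariates. The alternative is to stratify the baseline hazard by centre, with small centres pooled by a rule set in advance. Use the same model at both interim analyses, and fix the wording before any unblinded comparison. The frailty suits the first interim better: 110 × 0.75 ≈ 83 patients with insufficiency over 10 to 20 centres is only about 4 to 8 per centre, too thin for strata.

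Cost: centre is already recorded, so the frailty needs a short change of wording and slightly more analysis work. Strata instead of a frailty would cost about 1 to 2 points of power if centres turn out homogeneous, and cost 2.9 points in the 20-centre run without pooling.

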### Study protocol

Immediately after randomization, and before study drug administration, a short corticotropin test is performed (basal cortisolemia followed by 0.25 mg of synacthene ^® ^and cortisolemia on the 60^th ^min.). Patients are randomized to intravenous infusion of hydrocortisone (200 mg.day^-1 ^for 7 days, 100 mg on days -8 and -9, 50 mg on day-10) with enteral administration of fludrocortisone (50 μg.day^-1 ^for ten days) or to placebo. After receiving the results of the short corticotropin test (usually in the first 48 hours following inclusion), the treatment is stopped if patients have an adapted corticosteroid function.

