The selection of ICU patients who require hydrocortisone treatment is of particular importance. The concept of CIRCI has recently been introduced to differentiate the classical chronic corticosteroid insufficiency (Addison's disease) from the alteration of the hypothalamic-pituitary-adrenal axis observed in ICU patients [29]. CIRCI corresponds to an inadequacy between the severity of illness and the corticosteroid activity [19]. The combination of basal cortisolemia and/or a delta <9 μg/dl provides the best specificity and sensitivity for the diagnosis of CIRCI associated with severe sepsis [30]. Finally, recent recommendations have advocated use of either the basal cortisolemia or delta for diagnosis of CIRCI [31]. Regarding threshold of the basal cortisolemia, our definition is more liberal (<15 μg/dl) than the consensus statement (< 10 μg/dl). In the HYPOLYTE study using this liberal definition [10], patients with a normal corticosteroid function have a trend toward a decrease in rate of HAP as compared to patients with corticosteroid insufficiency treated with placebo (P = .06). Finally, the Corti-TC trial is not designed to test the accuracy of the CIRCI definition in trauma patients.

Despite inhibition of the cortisol synthesis, etomidate is recommended for Rapid Sequence Induction of multiple trauma patients [31]. For single bolus injection, the duration of adrenal blockade varies from 12 hours [32] to 24 hours [33], but it should be noted that this blockade was inconstantly reported [34]. In the Corti-TC study, a corticotropin test will not be performed within the first 8 hours following etomidate infusion and etomidate use in ICU is discouraged. Finally, as etomidate use may impact the results, etomidate will be considered as an effect modifier for the analysis (sensitivity analysis).

In conclusion, the Corti-TC trial is a nationwide investigator-initiated randomized controlled trial powered to test the hypothesis that the association of hydrocortisone with fludrocortisone in severe TBI patients prevents HAP. The Corti-TC trial also determines the effects of low dose of corticosteroids on duration of mechanical ventilation, length of ICU stay, organ failures and rate of death. An ancillary study will assess the long term neurological and psychological recovery of the included patients.

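### The ITT Cox model leaves out pre-dose corticosteroid-insufficiency status; the analysis is valid, but it may forgo a modest gain in power that costs almost nothing

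*Protocol article*

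**What the plan says.** The Statistical analysis section of the protocol article specifies a "Cox multivariate proportional hazards model that includes 2 predefined covariable: MGAP [15] and Coma Glasgow Score". Adjustment for etomidate is kept for sensitivity analyses. Hyporeactivity to ACTH appears as a subgroup, to be examined only if the primary endpoint shows a difference.

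The Study protocol section gives the timing of the adrenal test: "Immediately after randomization, and before study drug administration, a short corticotropin test is performed". Patients whose test shows adequate function then have study treatment stopped.

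The Discussion links the test result to the primary endpoint in two places. It argues that insufficiency worsens post-traumatic inflammation, which in turn favours infection. It also reports that, in the trial on which the sample size rests, patients "with a normal corticosteroid function have a trend toward a decrease in rate of HAP as compared to patients with corticosteroid insufficiency" on placebo, with P = .06. It gives no HAP rate for the normal-function group.

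The Statistical consideration section plans both an ITT and a mITT analysis, the latter in insufficient patients only, and does not say which is primary. On power it states: "The power calculation is performed for comparison between the hydrocortisone and placebo groups in patients with corticosteroid insufficiency".

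**The concern.** The test is drawn after randomization but before the first dose, in a blinded trial, so treatment cannot affect it. For adjustment purposes it is a baseline variable. The ITT population mixes insufficient and normal-function patients, assumed to be 75% and 25%. If the two groups differ in HAP risk, a Cox model that ignores the difference estimates a hazard ratio somewhat nearer 1 and has less power than a model that includes it.

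The ITT comparison is also the weaker of the two planned analyses, because about a quarter of its patients stop study drug early. Randomization is stratified by center and MGAP but not by insufficiency, so chance imbalance between the arms is possible and the planned model would not correct it. What is at stake is precision in the ITT result, not its validity.

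**Working it through.** **Inputs from the article.** Effect size and resulting number: "The sample size needed to detect an absolute decrease in pneumonia incidence of 20% is 121 patients in each group". The control-arm HAP rate behind that number is stated as: "assuming a rate of 70% in the placebo group". Error rates: "in a 2-sided test performed with a statistical power of 90% and an α risk of 5" percent. Insufficiency prevalence 75%, allocation 1:1, total 326, follow-up 28 days.

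**Reproducing the plan's figure.** With unpooled variance, n per group = (1.960 + 1.282)² × (0.70 × 0.30 + 0.50 × 0.50) / 0.20² = 120.8, that is 121 as stated. The pooled-variance formula gives 124. The total is 242 / 0.75 = 323, close to the stated 326. The inputs are therefore read correctly.

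**Hazard ratio in insufficient patients.** With exponential times, HR = ln(1 - 0.50) / ln(1 - 0.70) = 0.576.

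**Assumption.** The normal-function HAP rate is not in the article. It was taken as equal in both arms (no effect once drug is stopped) and varied from 20% to 70%.

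**Simulation.** Exponential times to HAP were censored at day 28, with N = 326 and 75% insufficient, two-sided 5% Wald test and 2000 trials per scenario. A Cox model with treatment alone was compared with treatment plus insufficiency status.

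| Normal-function HAP rate | Power without status | Power with status | Change (points) | HR without | HR with |
|---|---|---|---|---|---|
| 70% | 82.4% | 80.7% | -1.7 | 0.666 | 0.672 |
| 60% | 82.0% | 82.0% | 0.0 | 0.660 | 0.659 |
| 50% | 82.6% | 84.4% | +1.8 | 0.656 | 0.648 |
| 40% | 81.2% | 85.4% | +4.2 | 0.651 | 0.635 |
| 30% | 81.3% | 86.8% | +5.5 | 0.646 | 0.622 |
| 20% | 80.4% | 88.3% | +7.9 | 0.642 | 0.608 |

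The Monte Carlo standard error of a single power estimate is about √(0.82 × 0.18 / 2000) = 0.9 points. A separate simulation with 4000 trials per scenario gave 81% v 81%, 81% v 83%, 81% v 85% and 81% v 87% at rates of 60%, 50%, 40% and 30%.

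**Sensitivity.**
- The Abstract gives 376 patients, a discrepancy that is a separate matter. At N = 376 the changes are -1.6, -0.1, +2.6, +3.2, +4.1 and +6.4 points at rates of 70% down to 20%.
- If normal-function patients had the same HR of 0.576 as the others, power at N = 326 would go from 96.4% to 96.5%, 95.4% to 96.3%, 93.7% to 94.9% and 90.8% to 93.5% at rates of 60% down to 30%. The gain is then about 0 to 3 points.

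**mITT.** Status is constant within this set, so adding it changes nothing. Simulated mITT power at N = 326 is 91% to 92%, with HR about 0.575.

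**Where the ITT dilution comes from.** The HR moves from 0.576 in insufficient patients to about 0.65 in ITT because 25% of patients have no treatment effect in these scenarios. Adding status as a main effect moves it only from 0.656 to 0.648 at a 50% rate, or from 0.646 to 0.622 at 30%.

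**Chance imbalance.** With 163 per arm, the standard error of the between-arm difference in prevalence is √(2 × 0.75 × 0.25 / 163) = 4.8 points, so differences up to about 1.96 × 4.8 = 9 points are within the ordinary range.

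**The case against.** The strongest reply is that nothing here is an error. A randomized comparison adjusted for two predefined covariates is valid, and leaving out a third does not inflate type I error. A reader might infer that the ITT hazard ratio is biased toward 1. The article does not support that: the shift is non-collapsibility, meaning that the two models estimate different quantities, one less conditional than the other. This part of the reply stands in full.

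A reader might also infer that power is certainly lost. That does not follow either. The only quantitative evidence is a P = .06 trend from another trial, and the gain vanishes or turns slightly negative if normal-function patients have HAP rates of 60% to 70%.

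Nor is it right that the test result serves only to define the mITT set, since a conditional subgroup by ACTH hyporeactivity is also planned. And the trial is powered on insufficient patients, where restriction already deals with the status completely.

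Two practical objections also stand. The simulation compared models without MGAP and Glasgow score. If insufficiency tracks severity, the gain over the planned model would be smaller. Measured status may also partly reflect etomidate: the article requires 8 hours between etomidate and the test, while the Discussion cites blockade of 12 to 24 hours, and some patients may have no valid test. Neither objection makes a pre-dose value unsuitable as a covariate, but both limit what can be promised.

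What the reply does not remove is that the article fixes the covariate list itself, treats insufficiency as related to HAP, plans an ITT analysis without ranking it below the mITT, and leaves a pre-dose measurement that is already collected out of that model.

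**Conclusion.** The point holds as an efficiency improvement to the ITT analysis, not as a flaw that invalidates it. Over the assumed normal-function HAP rates of 30% to 60%, including insufficiency status changes ITT power at N = 326 by about 0 to 6 points and lowers the estimated HR by at most 0.024. If the normal-function rate equals the 70% assumed for insufficient placebo patients, power falls by about 2 points.

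These figures rest on the plan's own 70% versus 50% and 75% prevalence, on no effect in normal-function patients, and on a normal-function rate that the article does not state. MGAP, Glasgow score, deaths and the interim looks were not modelled. It would be wrong to read the covariate as a cure for the dilution caused by stopping drug in a quarter of the patients: most of that dilution remains after adjustment.

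**What to change.** Before any unblinded look, add pre-dose corticosteroid-insufficiency status, coded as insufficient, normal or no valid test, as a third predefined covariate or as a stratum in the ITT Cox and Fine and Gray models for HAP. The third level keeps every randomized patient in the analysis. Leave the mITT model unchanged. The Trial status section places the first interim analysis in November 2011, so the change should be dated before that look.

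The cost is one line of text and one or two degrees of freedom, with no new data collection. The downside is a possible power loss of about 2 points if the status turns out not to be prognostic.

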### Study end points

Primary endpoint is the occurrence of HAP within 28 days of randomization. Pneumonia is considered when at least 2 signs (body temperature > 38°C; leukocytosis >12 000/mL, or leukopenia <4000/mL; purulent pulmonary secretions) associated with the appearance of a new infiltrate are present or when changes occur in an existing infiltrate on chest x-ray. The diagnosis needs to be confirmed by a respiratory tract sample using a quantitative culture with a predefined positive threshold of 10^4 ^colony-forming units per milliliter (CFU/mL) for a bronchoalveolar lavage or non bronchoscopic sample, of 10^3 ^CFU/mL for a protected specimen brush and of 10^6 ^CFU/mL for a tracheal sample. Hospital-acquired pneumonia is defined as pneumonia that occurs 48 hours after admission that had not been incubating at the time of admission.

The secondary outcomes are duration of mechanical ventilation and length of ICU stay, antibiotic free days, rate of death, other infections, organ failures, and duration of vasopressor support on day 28 and in ICU. Safety is assessed by recording adverse events.

An ancillary study will assess the mortality, the long term neurological and psychological recovery on the -6^th ^and -12^th ^month.

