### Follow up

The following variables are collected: demographics, Apache 2, MGAP score [15], injury severity score and abbreviated injury score, fluid infusions, vasopressors, antibiotherapy, etomidate use, surgery, intracranial pressure, infections, organ failures, natremia, length of ventilatory support, and ICU hospitalisation and death in ICU and at day 28 are recorded. In ICU, clinical assessments are performed at least twice a day. Clinical evaluation for diagnosis of pneumonia are performed twice a day in the ICU. A chest x-ray is performed as soon as pneumonia is suspected after clinical examination. A respiratory tract sample is collected for bacteriological analysis before any modification of antibiotic therapy. Patients or relatives are contacted on -6 and -12 month for evaluation of neurological recovery (GOS, Kartz index), of quality of life, of depression disorder (HAD scale, SF-36 and I.E S-R scores) and of mortality.

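### The only methods named for the secondary endpoints let an early death count as a short ventilation, ICU or vasopressor duration, so any mortality difference biases those comparisons

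*Protocol article*

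**What the plan says.** The section Study end points gives the list: "The secondary outcomes are duration of mechanical ventilation and length of ICU stay, antibiotic free days, rate of death, other infections, organ failures". The last item in it is vasopressor support, which is again a length of time. Ventilation, ICU stay and vasopressor support thus all appear there as durations. Only antibiotic use is expressed as free days.

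The section Statistical analysis has one sentence on method for all of these: "Linear or logistic regressions will be used as appropriate for the secondary endpoints". The same section deals with death explicitly, but for pneumonia only: "Cumulative incidence will also be estimated for the primary outcome by treating deaths as competing risks", followed by the Fine and Gray model.

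Under Follow up, the recorded items include the length of ventilatory support, vasopressors, "and ICU hospitalisation and death in ICU and at day 28 are recorded". The conclusion of the Discussion says that the trial "also determines the effects of low dose of corticosteroids on duration of mechanical ventilation, length of ICU stay, organ failures and rate of death", so the duration results are meant to be read as treatment effects.

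**The concern.** Each of these durations can end in two opposite ways: the patient recovers, or the patient dies. A linear regression of days sees only the length. A death on day 4 scores the same as a successful extubation on day 4, and better than a survivor extubated on day 15. If one arm has more early deaths, its mean duration falls without any patient being weaned sooner. If one arm has fewer, its mean duration rises and a treatment that saves lives appears to prolong ventilation.

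Enrolment requires a Glasgow Coma Scale score of 8 or less, and death is itself a listed outcome, so deaths during ventilation and ICU stay must be expected. The authors recognise the problem for pneumonia and hold the tool for it, but confine it to that endpoint. What is at stake is the meaning of the estimates and p-values for three secondary endpoints.

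**Working it through.** **What the text fixes.** Two method classes are named. Logistic regression needs a binary outcome, so a duration in days falls to linear regression. Neither class separates ending by recovery from ending by death.

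**The plan's own figure.** The article gives no number for the duration endpoints. The check borrows its group size of 121 (patients with corticosteroid insufficiency), which reproduces with unpooled variance: (1.960 + 1.282)² × (0.70×0.30 + 0.50×0.50) / 0.20² = 10.51 × 0.46 / 0.04 = 120.8, hence 121.

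**Assumed inputs (none are in the documents).**
- Time to end of ventilation, V: log-normal, median 12 days, log-SD 0.7, capped at 28 days, identical in both arms. Its mean is E[V] = 13.82 days.
- Time to death among those who die, T: exponential, mean 5, 8 or 12 days.
- Control mortality 20%; active arm 25% or 30%.

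**Formula.** With mortality p, the mean recorded duration is (1 − p)·E[V] + p·E[min(V,T)]. With the same V and T in both arms, an excess mortality Δ produces a spurious difference of

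−Δ × (E[V] − E[min(V,T)]).

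The standard error is SD × √(2/121) = SD × 0.1286. The within-arm SD is about 8.1, 7.95 and 7.85 days for the three death times. The chance of a significant false benefit is about Φ(−1.96 + |difference|/SE).

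| Mean time to death | E[min(V,T)] | Gap to 13.82 | Δ = 5 points | Δ = 10 points | SE | False benefit, 5 points | False benefit, 10 points |
|---|---|---|---|---|---|---|---|
| 5 d | 4.27 | 9.55 | −0.48 d | −0.95 d | 1.04 | 6.6% | 14.8% |
| 8 d | 5.93 | 7.89 | −0.39 d | −0.79 d | 1.02 | 5.8% | 11.8% |
| 12 d | 7.45 | 6.37 | −0.32 d | −0.64 d | 1.01 | 5.0% | 9.2% |

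For example, in the first row Φ(−1.96 + 0.95/1.04) = Φ(−1.05) ≈ 0.148. A simulation of 20,000 trials per cell with a two-sample t-test (the same as linear regression on arm) agrees to within 0.3 percentage points. With no mortality difference it returns about 2.5%, as it should.

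**The same patients scored as ventilator-free days to day 28, death = 0.** The mean is (1 − p)(28 − 13.82), so the difference is −Δ × 14.18: −0.71 days at 5 points and −1.42 days at 10 points. The sign now points to harm. A false significant benefit appears in about 0.5% of simulated trials at 5 points and under 0.1% at 10.

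**Sensitivity to the assumptions.** A second set (median ventilation 16 days, log-SD 0.6, mean time to death 4 or 8 days, control mortality 15 to 25%) gives a spurious shortening of about 1.0 to 1.4 days at 10 points of excess mortality and a false benefit in about 16 to 23% of trials. The direction is the same; the size depends on the inputs. By the formula, lower mortality on treatment gives the mirror image, an apparent lengthening.

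**The case against.** **The text does not say raw durations.** This is correct. It assigns no method to a named endpoint, and the full protocol or analysis plan may say how deaths enter. A missing death rule in a condensed article would be no finding. What remains is the method class that is stated. Regressing survivors only would not rescue it, because that conditions on an outcome that treatment may change. Free days would go a long way, but the article uses that form for antibiotics and not for these three endpoints.

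**Mortality is reported separately.** This also stands, and it limits the harm. A reader might infer that a harmful treatment could pass as beneficial overall. The documents do not support that: death is a secondary outcome, recorded in ICU and at day 28 and followed to 12 months, so excess deaths would be visible. They would not, however, correct the duration estimate or its p-value.

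**The size rests on assumptions.** It does. At 121 per arm the bias is at most about one standard error in the main illustration.

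Two further readings are tempting and do not hold. One is that the Discussion's defence of pneumonia as primary endpoint depends on this trial's duration results. It cites the durations seen in the earlier hydrocortisone trial in multiple trauma, which this trial's analysis cannot affect. The other is that the Kaplan-Meier estimates for pneumonia are a fault as well, because they censor deaths. They are an additional display ("The crude percentages and the Kaplan-Meier estimators will also be presented"), and cumulative incidence with the Fine and Gray model is already planned for that endpoint.

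**Conclusion.** The point holds for the three duration endpoints and no further. The only methods named for them do not distinguish recovery from death, although the plan makes that distinction for pneumonia. On the natural reading, linear regression of days, a mortality difference biases the duration comparison.

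Under the main assumptions, 5 to 10 points of excess mortality produce a spurious shortening of about 0.3 to 1.0 day and raise the chance of a false significant benefit from 2.5% to about 5 to 15%. Later deaths make it smaller; earlier deaths or longer ventilation make it larger. If mortality and its timing are equal in the arms, this bias disappears. The primary pneumonia analysis is unaffected. This is a change worth making to secondary endpoints, not a flaw that threatens the trial's main result.

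**What to change.** In Study end points and Statistical analysis, replace the three durations as tested endpoints by one of these:

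1. Ventilator-, ICU- and vasopressor-free days to day 28, with patients who die by day 28 scored 0, compared by a rank-based test.
2. Time to liberation from ventilation, ICU discharge alive and end of vasopressor support, with death as a competing event, using the Fine and Gray model already in the plan.

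In either case show the result beside mortality. The durations themselves may stay as descriptive summaries. The choice should be fixed before any comparison by arm is seen.

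The cost is mainly wording. Free days mix mortality with duration, so a difference needs the mortality result to be understood. The competing-event option needs the dates on which ventilation, ICU stay and vasopressors end. Follow up lists lengths and death status but does not mention such dates, so their availability should be confirmed before choosing it.
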